#### **Secondary objectives**

Predictor analysis

To evaluate whether selected radiological parameters and patient characteristics measured at baseline can predict outcomes, and thereby also used to choose the most appropriate treatment.

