#### **Radiological evaluations:**

Radiological evaluations will be performed by independent investigators.

Preoperative and 3 months postoperative MRI scans will be evaluated to measure the extent of decompression by calculating the change in dural sac cross-sectional area at the most stenotic level (square millimetres [16]. The association between the increase in dural sac cross-sectional area and clinical improvement (primary outcome) will be assessed. We will compare the increase in dural sac cross-sectional area in patients who achieve a minimal clinically important change of the ODI with those who do not.

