## **Statistical analyses**

All statistical analyses will be performed by a statistician blinded to the treatment given. Since this is a large randomized controlled trial, we will likely not need to adjust for potential confounding factors. However, if descriptive statistics reveal that there are imbalances in the study groups we will make comparisons with proper adjustments for such imbalances.

When comparing changes in outcomes from baseline to a fixed time point (e.g. 2, 5 or 10 years) we will use ANOVA combined with post-hoc testing for continuous outcomes. For categorical outcomes we will use standard chi-square analyses. If there is a need for confounder adjustment we will estimate the proper regression models dependent on the level of measurement of the dependent variable. Multilevel models might be used to analyse repeated measures data.

When trying to identify factors that could serve as predictors for outcome we will estimate multivariable regression models. The following factors are a priori considered to be the most relevant: treatment group, age, sex, BMI, smoking, preoperative dural sac cross-sectional area (in mm^2), percentage achieved decompression, preoperative ODI-score and preoperative NRS-score for leg pain and back pain. Bayesian information criterion (BIC) might be used as a statistical tool to select the best performing model.

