## **Radiological results**

Studies have been conducted to identify objective radiological criteria for LSS [32]. We have chosen to investigate the Dural Sac Cross Sectional Area (DSCSA). This is measured at the disc level where the narrowest stenosis occurs. DSCSA can be measured both on a CT-scan and MRI-scan [22,28-30]. The normal population is reported to have a DSCSA of about 170 mm^2. In the studies quoted, moderate stenosis was defined as a DSCSA between 70 and 100 mm^2, and significant stenosis as an area below 70 mm^2. One study found a significant correlation between DSCSA and clinical symptoms, but one other study did not confirm this. Both of these studies included a relatively small number of patients (n=109) [29]. Our previous study [16], has shown a positive correlation between an increase in the DSCSA and improvement in clinical symptoms. To our knowledge this has not been documented before. At present, we cannot identify a threshold value in the spinal canal area that gives clinical symptoms. Neither can we identify a minimal increase in area that is needed to give long-term relief of symptoms. We hope to be able to answer these questions. Our previous study showed an increase in DSCSA using SPO of 101%, up to an average area of 161 mm^2 postoperatively [16]. Dalgic et al compared “bilateral laminotomy” and unilateral laminotomy with crossover”, and found a postoperative area of 126 mm^2. This is significantly lower than the area found when SPO is used. We are therefore planning to measure DSCSA before and after surgery, to see whether there are differences between the three different surgical methods. We also want to investigate whether there is a correlation between achieved increase in area and the patients’ self-evaluated outcome of surgery.

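### The SAP's predictor models list a postoperative variable beside treatment group and name no technique-by-baseline interaction, which does not fit an objective of predicting from baseline data to help choose treatment

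*Combined protocol and SAP*

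**What the plan says.** **Objective.** The SAP's Secondary objectives describe a predictor analysis. It asks whether radiological parameters and patient characteristics "measured at baseline can predict outcomes, and thereby also used to choose the most appropriate treatment".

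**Model.** SAP section 4, Statistical analyses, plans multivariable regression models and lists the factors judged most relevant in advance. The list starts with "treatment group, age, sex, BMI, smoking, preoperative dural sac cross-sectional area" and goes on to "percentage achieved decompression, preoperative ODI-score and preoperative NRS-score for leg pain and back pain". It adds that "Bayesian information criterion (BIC) might be used as a statistical tool to select the best performing model". No product of treatment group with another factor is named.

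**When decompression is measured.** The SAP's Radiological evaluations state: "Preoperative and 3 months postoperative MRI scans will be evaluated to measure the extent of decompression". The same section plans a separate analysis of the association between the increase in dural sac area and clinical improvement.

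**The research protocol's list.** Supplementary analysis I plans logistic regression of 24-month success on treatment group, hospital and preoperative characteristics. Achieved decompression is not among them, and again no interaction is named.

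**The concern.** There are two mismatches between the stated objective and the listed factors.

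1. **Timing and causal position.** A variable known only after surgery cannot inform the choice of operation. It is also a plausible consequence of the technique. If it sits beside treatment group in one model, the treatment coefficient leaves out whatever part of the technique effect acts through decompression. It also becomes exposed to unmeasured causes shared by decompression and outcome, because randomisation does not protect a comparison made at equal decompression.
2. **No interactions.** Prediction of who does well and selection of a technique for a given patient are different questions. The second needs terms that let the technique difference vary with baseline characteristics.

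At stake is a published secondary model that could be read as evidence on treatment selection, or whose treatment coefficient could be read as the technique effect, when it is neither.

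**Working it through.** **1. Is the listed variable postoperative?** Yes. Radiological evaluations derive the extent of decompression from preoperative and 3-month scans. The SAP Timeline adds MRI at 2 and 5 years, also after surgery. The percentage itself is not defined, since that section describes a change in square millimetres. If it is the change divided by the preoperative area, as seems likely, its denominator is another listed factor.

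**2. Is it a candidate mediator on the documents' own reasoning?** Yes. The protocol's Radiological results supply both links.
- Technique to decompression: "an increase in DSCSA using SPO of 101%, up to an average area of 161" mm², against a cited comparison of the two laminotomies that "found a postoperative area of 126" mm², which the protocol calls significantly lower.
- Decompression to outcome: the group's previous study is reported as showing a positive correlation with clinical improvement.

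**3. How far could the treatment coefficient move?** The documents give no slope of ODI on decompression, so this step is an illustration under assumptions.
- Implied preoperative area for SPO: 161 / 2.01 = 80.1 mm².
- If the laminotomy patients started from the same area (an assumption across two studies): 126 / 80.1 − 1 = 57%.
- Gap between techniques: 101 − 57.3 = 43.7 percentage points.
- Take a total technique effect of 7 ODI points. This is the design difference, not an expected effect.
- With no shared unmeasured cause, adjusted coefficient = 7 − slope × 43.7.
- With an assumed unmeasured factor, suppose one SD of it adds 20 percentage points of decompression and 5 ODI points of improvement, and other variation in decompression has SD 35. The fitted slope then gains 20 × 5 / (20² + 35²) = 0.0615, and the coefficient falls by a further 0.0615 × 43.7 = 2.7.

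| Assumed slope (ODI points per percentage point) | Adjusted, no shared cause | Adjusted, shared cause |
|---|---|---|
| 0 | 7.0 | 4.3 |
| 0.025 | 5.9 | 3.2 |
| 0.05 | 4.8 | 2.1 |
| 0.10 | 2.6 | −0.1 |
| 0.16 | 0.0 | −2.7 |

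If the shared cause acted on outcome in the opposite direction, the 2.7 would be added instead, giving 9.7 at slope 0. Neither size nor direction is fixed by the documents, and no change at all is possible.

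**4. Can a main-effects model select a technique?** In a linear model, predicted outcome = a + τ(technique) + βx. The difference between two techniques is τ₁ − τ₂ whatever x is. In a logistic model the log-odds difference is likewise constant, so the ranking of techniques is the same for every patient.

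**5. What could interactions deliver at this sample size?** First, the plan's own figure:
- n per group = 2 × [18 × (2.326 + 0.842) / 7]² = 132.7, so 133, against 131 in the protocol's Statistics section.
- 131 / 0.85 = 154.1, so 155 as stated. 131 / 0.70 = 187.1, which matches the stated 187.

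The inputs therefore reproduce closely with two-sided alpha 0.02. Now take one pairwise technique contrast with a binary baseline factor split 50:50 (an assumption) and 131 evaluable per arm:
- SE of the interaction = 2 × 18 × √(2/131) = 4.45 ODI points.
- Power = Φ(interaction / 4.45 − 2.326): 23% for 7 points, 47% for 10, 79% for 14.
- Interaction detectable with 80% power: 4.45 × 3.168 = 14.1 points.
- Evaluable patients per arm needed for 7 points: 8 × [18 × 3.168 / 7]² = 531.

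These are single-contrast figures, not the power of a joint 2-df test.

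**The case against.** Much can be said for the plan.

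- **It is a candidate list, not a fixed model.** The SAP speaks of models in the plural and allows optional BIC selection. It does not say that treatment group and achieved decompression must be fitted together, and it does not rule out interactions. This stands, so the criticism is of what is listed and left unspecified. But BIC selects on fit, not on timing or causal role. It could keep decompression and drop treatment group. Interactions chosen after seeing data would be post hoc.
- **Decompression has a legitimate role.** The SAP's Main Objective also asks how much decompression is required for lasting good results, and Radiological evaluations plan an association analysis for it. This stands too. It gives the variable a home elsewhere and does not require it in a model for preoperative use.
- **The protocol already has a list without it.** True of Supplementary analysis I, and the SAP calls itself a supplement to the protocol. Whether that analysis still applies alongside the SAP's list is unclear.
- **Interactions would be underpowered.** Correct, as shown above. They should therefore be exploratory, but low power does not make a main-effects model answer the selection question.

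A reader might infer that the trial's estimate of the technique effect is biased, or that it would shrink by half or to zero. The documents do not support either reading. The primary comparison is ANOVA with post-hoc tests and does not include decompression. Nothing says that the predictor model's coefficient will be reported as the technique effect. Any stated shrinkage only restates an assumed slope or mediated share.

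**Conclusion.** The concern holds as a mismatch in a secondary analysis. A postoperative variable is listed with treatment group for models whose stated objective is baseline prediction to help choose treatment. Any model containing both cannot be applied before surgery, and its treatment coefficient is not the total technique effect. How far the coefficient would move cannot be derived from the documents; the table in the working spans no change to a change of sign, all under assumed inputs. With no interaction specified, a main-effects model restricted to baseline variables can meet the prognostic half of the objective, but it cannot show which technique suits which patient. The randomised primary comparison is unaffected. Severity is minor to moderate.

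**What to change.** 1. **Baseline predictor model.** Restrict the model serving the Secondary objectives to baseline variables plus treatment group. Remove achieved decompression, in line with the protocol's Supplementary analysis I.
2. **Interactions.** Pre-specify a short list of technique-by-baseline terms, for example with baseline ODI, preoperative dural sac area and age; the final choice is the trial team's. Test each with a joint 2-df test, report estimates with confidence intervals, and label the set exploratory.
3. **Decompression.** Keep achieved decompression in the association analysis already planned under Radiological evaluations, serving that part of the Main Objective. Define the measure, adjust for preoperative area, baseline ODI, age and arm, and label the result non-randomised.

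The cost is SAP wording and some extra analysis; no new data are needed. The downside is low interaction power. An inconclusive interaction test should not be reported as evidence that the techniques suit all patients equally.

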## **5) Trial population**

Patients will be recruited by each of the participating hospitals. If there is an indication for bilateral decompression of the spinal canal, and the patient is referred for surgical treatment to one of the participating hospitals, the patient is eligible for inclusion in the study. Inclusion and exclusion criteria are evaluated, and the patient is invited to participate in the study if all inclusion criteria and no exclusion criteria are present. If the patient agrees to participate, he or she will be randomized into one of the three surgical procedures. The patients should have an MRI-scan, and a x-ray of the lumbosacral spine, taken up to 6 months earlier.

**Inclusion criteria:**

- have clinical symptoms of spinal stenosis as neurogenic claudication or radiating pain into the bilaterally to the lower limbs,
- -not responding to at least 3 months of non-surgical treatment.
- -radiological findings corresponding to the clinical symptoms of LSS. Central-stenosis, or lateral recess-stenosis.
- be able to give informed consent and to answer the questionnaires.
- -over 18 years of age
- be able to understand Norwegian language, spoken and in writing

**Exclusion criteria:**

- have a degenerative lumbar spondylolisthesis, with a slip  $\geq 3$  mm verified on standing plain x-rays in lateral view.
- -are not willing to give written consent.
- -have former surgery in the level of stenosis.
- -fracture, or former fusion of the thoracolumbal region.
- -cauda equina syndrom (bowel or bladder dysfunction) or fixed complete motor deficit.
- -are ASA- classified 4 or 5.
- -are older than 80 years
- -have a lumbosacral scoliosis more than 20 degrees verified on AP-view
- -have **distinct** symptoms in one or both of their legs due to other diseases, e.g. polyneuropathy, vascular claudication or osteoarthritis.
- -LSS in 4 or more levels.

- -not able to comply fully with the protocol, including treatment, follow-up or study procedures (psychosocially, mentally and physical).
- the patient is participating in another clinical trial that may interfere with this trial

## **Timeline:**

### **Before operation:**

- Skeletal X- rays.
- MRI- scan for measuring preoperatively DSCSA.
- Following completion of the consent form the following PRO- data will be collected: ODI, ZCQ, EQ- 5D, HSCL 25, VAS for back- and leg-pain demographics, work status, smoking status and use of analgesics.

### **During the hospital stay:**

- The surgeon will register radiological findings, ASA-classification, operation method, operation time, level and blood loss, and per-operative complications.
- Complications will be registered during follow-up by an independent nurse or physician.

### **3 months postoperatively ( $\pm$ 2 weeks):**

- The following PRO- data will be collected: Working status, ODI, ZCQ, EQ-5D, VAS for back- and leg-pain, patient satisfaction with treatment outcome, and patient satisfaction with treatment care.
- MRI scan to measure DSCSA postoperatively.

### **12 months postoperatively ( $\pm$ 1 month):**

- -The same PRO-data as at 3 months will be collected.

#### **2 years postoperatively (± 2months):**

- -The same PRO- data as at 3 months will be collected.
- MRI scan to measure DSCSA.
- -Skeletal x-rays: standard images will be performed.
- -CT- scanning for examining the union of the spinous process (only the SPO-group).

#### **5 years postoperatively (± 3 months):**

- -The same PRO-data as at 3 months will be collected.
- MRI scan to measure DSCSA.
- -Skeletal x-rays: standard images will be performed.

#### **10 years postoperatively (± 3 months):**

- -The same PRO-data as at 3 months will be collected.
- Skeletal x-rays: standard images will be performed.

# Norwegian Spinal Stenosis Study Research Protocol

## **Comparison of different surgical treatments for Lumbar Spinal Stenosis. A randomized controlled trial comparing the clinical and radiological results using “spinous process osteotomy”, “bilateral laminotomy” and “unilateral laminotomy with crossover”.**

This is planned to be a multicenter study with 15 participating Norwegian spine centers. The departments of orthopedics at Oslo University hospital and Kysthospitalet i Hagevik, Haukeland University hospital, will be the principal investigators. Two MDs are connected to the study as doctoral students.

## **Background, introduction and hypothesis**

Surgery for Lumbar Spinal Stenosis (LSS) is the most frequently performed procedure today on the adult lumbar spine [4]. The clinical entity “Lumbar Spinal Stenosis” can be defined as a narrowing of the lumbar spinal canal with its contents. This leads to compression of nervous and vascular structures. LSS is a degenerative condition where the patho-anatomic change involves a bulging disc, hypertrophy of the ligamenti flavi and hypertrophy of the facet-joints. The symptoms are most commonly neurogenic claudication, or sciatic pain, and Low Back Pain. The most stenotic part is at the disc-level. Several studies with long-term follow up have been performed to evaluate surgical treatment versus non-surgical treatment [1,20,36], and they conclude that surgical intervention gives superior results. The surgical procedure performed in these studies is a laminectomy. A Cochrane review article also concludes that surgery is superior to non-surgical treatment [12].

The surgical treatment of LSS is to perform a decompression. To achieve relief of the stenosis, one must remove the flaval ligaments, and the lamina (whole, or parts of it) at the disc level, and carry out a partial medial facetectomy to decompress the nerve-root in the lateral recess. The traditional operation is a laminectomy, which involves the total removal of the lamina and the flaval ligaments, with a medial facetectomy. This procedure also removes much of the posterior ligamenture of the spine, and is considered to be a relatively invasive procedure; it is also prone to postoperative instability of the operated spinal segment. In recent decades bilateral laminotomy has become an alternative to a laminectomy [2,19]. This is a less invasive procedure, in which parts of the lamina are retained, and the interspinal and supraspinal ligaments are mostly kept intact. This procedure is therefore considered to be better at preserving stability. More recently a unilateral decompression has been described [21], referred to as a “bilateral laminotomy with crossover technique”. The access to the spinal canal is unilateral, and the ipsilateral side is decompressed as usual, whereas the contralateral side is decompressed using a crossover technique. This has theoretical advantages by preserving more of the paraspinal muscles, ligaments and bony structures. A third alternative is to do a spinous process osteotomy [13]. This procedure also involves unilateral release of the paraspinal muscles, and an osteotomy of the spinous process at the

base, above the actual level. These osteotomies facilitate access to the spinal canal with improved visibility, which may be an advantage over the other methods.

Several studies have been conducted to compare laminectomy and bilateral laminotomies [3,8,11,24,26,34,35]. A Cochrane review article from 2005 state that one cannot conclude which procedure gives superior clinical results in these studies [12]. In our opinion later studies have not fulfilled this purpose either. Some studies compare “bilateral laminotomy” with “unilateral laminotomy with crossover”. One of these studies shows inferior results with “unilateral laminotomy with crossover” [35], and two studies show equal clinical results between the two procedures [6,17]. There are no studies comparing spinous process osteotomy with other procedures.

Therefore, we plan to perform a multicentre, randomized trial to compare the clinical and radiological results of “spinous process osteotomy” (SPO), “bilateral laminotomy” (BL), and “unilateral laminotomy with crossover” (UL).

## Clinical results

The main goal of this study is to identify which method gives the best long-term clinical results, including the most pain reduction and the best functional results. The patient’s own, self-evaluated assessment of the surgical procedure is the most important outcome. Today, there are several questionnaires that are used to map the clinical status of the patient. The patient answers a questionnaire before the surgical procedure, and the same questionnaire is repeated after surgery, to monitor the effect of the surgical treatment. We have decided to use the same questionnaires that the Norwegian Quality Register for Spinal Surgery (NORSPine) uses, and thus cooperate with the register when collecting data postoperatively. These questionnaires consists of the Oswestry Disability Index (ODI), EQ-5D, Numeric Rating Scale (NRS) for low back pain (LBP), Numeric Rating Scale (NRS) for leg-pain, and the patient’s self-evaluated effect of surgery. These questionnaires have been evaluated in several studies [7,9,10,15,31]. They give an evaluation of the patient’s pain situation, level of function, perceived quality of life, and the self-assessed effect of the surgical treatment. In addition we will use the Swiss Spinal Stenosis Questionnaire (SSSQ). This questionnaire is considered more specific to spinal stenosis, and has also been evaluated in several studies [25,33].

In recent decades the ODI has had a special status within spinal care. There are hardly any studies where clinical results are monitored without this questionnaire. In this questionnaire ‘0’ is the best status, and ‘100’ is the worst status. The desired effect of surgical treatment is a significant decrease in the patient’s ODI-score. We have therefore chosen the ODI as a primary outcome of this study. This application aims to reveal the 10 year improvement in ODI related to the three different surgical methods. When using the ODI as a primary outcome, it is important to decide beforehand what is to be regarded as a significant improvement in the score following surgical treatment. This is now discussed as the Minimal Clinically Important Difference (MCID). MCID is measured as the difference in the mean ODI-scores of patients that score “some improvement” compared with those who score “no improvement”. This value has been found to be 10-12 ODI-points [5,14,23].

